### Interventions

#### Telephone counselling condition

The national German Smokers Quitline offers telephone counselling to smokers seeking support in smoking cessation, to former smokers experiencing a relapse crisis, and to information seekers. The majority of counsellors are non-academic health professionals such as nurses. Counsellors receive an intensive three-day training following the WHO training protocol “Quitline Counselling” which includes amongst other things the training on the used counselling software, the simulation of calls as well as on-site observation of experienced counsellors.

The counselling follows a structured, yet flexible counselling protocol based on the protocol of the California Smokers’ Helpline [14]. The principles of this protocol are built upon the theory of social learning [22, 23], which emphasizes the client’s capacity for self-regulation and the relevance of self-efficacy in behaviour change [14]. Therefore, the protocol combines the principles of motivational interviewing (MI) (Miller & Rollnick, 1991) and those of the cognitive behavioural approach to treating substance use e.g. [14, 24]. MI is used to induce behaviour change by enhancing the client’s intrinsic motivation to change. An empathetic, non-confrontational conversation style generates a collaborative counsellor-client relationship and allows to address the clients` ambivalence [25]. Once a client is ready to quit smoking, the counsellor applies cognitive-behavioural strategies. The client is encouraged to identify and restructure dysfunctional cognitions about smoking and quitting and to develop and implement coping strategies [14, 26]. A central tenet of this complementary approach is the counsellor’s continuous monitoring and fostering of the client’s motivation to quit and the support to increase self-management skills and self-efficacy to change [14]. Adherence to the counselling protocol is assessed on a regular basis by analyzing recorded calls and digital counselling notes taken by the counsellors.

In the telephone condition, based on their needs, participants can receive up to six proactive phone calls (14, for detailed information see 19). The first session (intake session) will take 20 to 25 minutes and will focus on assessing the client’s smoking and quitting history, their smoking habits and their motivation to quit. Moreover, the counsellor aims to resolve ambivalent feelings, to strengthen the client’s self-efficacy and motivation to quit, to identify difficult situations and to develop strategies for coping with the urge to smoke. Finally, the counsellor will encourage the client to set a quit date within the next 14 days. Participants are then offered up to five follow-up calls to support relapse prevention and the maintenance of smoking cessation. The first follow-up session will take place approximately two to three days after the quit date, the second will take place approximately seven days after the quit date; the third approximately twelve days, the fourth approximately three weeks and the fifth follow-up call approximately one month after the quit date. These sessions take about ten minutes each and cover the following topics: Assessing the client’s progress and evaluating the effectiveness of applied coping strategies, discussing withdrawal symptoms, the urge to smoke and self-efficacy as well as examining difficult situations and their handling.

#### Self-help condition

In the control condition, participants will receive the self-help brochure ‘Ja, ich werde rauchfrei!’ [‘Yes, I’ll be smoke-free’] which is being disseminated by the Federal Centre for Health Education [27]. The 92-page booklet is directed at individuals attempting to achieve smoking cessation. It follows the principles of cognitive-behavioural therapy [26] and guides the reader step by step from preparing to quit to long-term abstinence. The brochure is divided into the parts: information about smoking and smoking cessation, preparing and planning for smoking cessation and information on topics related to maintaining abstinence (e.g., anticipation of potential high-risk situations, smoking urges, developing the identity of a non-smoker, use of cognitive and behavioral coping responses, keeping weight gain in perspective, finding other forms of positive reinforcement, management of stress). Participants in the control condition will be offered telephone counselling at the end of the study.

### Outcomes

Outcome measures and covariates with their respective assessment time points are shown in Table 1.

**Table 1 Tab1:** Standard Protocol Items: Recommendations for Interventional Trials (SPIRIT) diagram

	STUDY PERIOD						
	Recruitment	Enrolment	Allocation	Post-allocation			
TIMEPOINT	-t_2_	-t_1_	0	t_1_	t_2_	t_3_	t_4_
	Screening	Baseline assessment	Randomization	Intervention	Post assessment	Follow-up assessment	Biochemical verification
**ENROLMENT:**							
**Eligibility screen**	X						
**Informed consent**	X	X			X	X	X
**Randomization**			X				
**INTERVENTIONS:**							
**Telephone counselling**				X			
**Self-help brochure**				X			
**ASSESSMENTS:**							
**Socio-demographic characteristics**	X	X					
**Smoking-related variables**		X			X	X	
**Health status**		X			X		
**Received social support**					X		
**7-day point prevalence abstinence**					X	X	
**Prolonged abstinence**						X	
**Number of cigarettes smoked per day**	X	X			X	X	
**Nicotine dependence**		X			X	X	
**Number and duration of quit attempts**					X	X	
**Occurrence of abstinence of at least 24 hours**					X	X	
**Motivation to quit**	X	X			X	X	
**Implementation of smoking restrictions at home**		X			X	X	
**Smoking-related cognitions**		X			X		
**Coping strategies**		X			X		
**Use and acceptability of the received intervention**					X		
**Breath carbon monoxide (CO)**							X

Note: -t2: recruitment of participants by a market research company using a screening questionnaire; −t1: baseline assessment; 0: randomization of participants to either the intervention or control condition; t1: intervention (telephone counselling or self-help broschure); t2: post assessment 3 months after baseline assessment; t3: follow-up assessment 12 months after baseline assessment; t4: biochemical verification: 20% random sample of participants who reported 7-day point prevalence abstinence at 12-month assessment

#### Primary outcomes

In accordance with the Russell standard criteria [28], primary outcome measures will include (1) seven-day point prevalence abstinence at 3-month post and 12-month follow-up assessment, (2) prolonged abstinence (abstinence over the 12 month period allowing up to five cigarettes in total), and (3) biochemical verification of abstinence in 20% of the abstainers at 12-month follow-up. To define abstinence, cut-off scores of 8 ppm for CO will be used [29].

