**Methods:**

A total sample of 910 daily smokers, who are motivated to quit, will be recruited via an online access panel and randomly assigned to either the intervention (telephone counselling) or control condition. In the intervention group, participants will receive up to six proactive phone calls during an intervention period of approximately six weeks. The provided treatment will combine the principles of motivational interviewing and those of the cognitive behavioural approach to treating substance use. Participants in the control condition will receive a self-help brochure to support smoking cessation. Data collection will take place at baseline as well as three (post assessment) and twelve months (follow-up assessment) after baseline assessment. Primary outcome measures will include the seven-day point prevalence abstinence at 3-month and 12-month assessments as well as prolonged abstinence (abstinence over the 12 month period). Secondary outcome measures will include a change in smoking-related cognitions and coping strategies among all participants. Among non-abstainers, treatment success indicators such as a reduction in number of cigarettes smoked per day and changes in the number and duration of quit attempts after intervention start will be assessed. It is expected that after both three and twelve months, smoking cessation rates will be higher in the telephone counselling condition compared to the control condition.

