## Methods

### Study design

The present evaluation is designed as a parallel-group, superiority, two-arm randomized controlled trial with 1:1 allocation ratio. The evaluation comprises three assessments within a period of approximately one year. Data collection will take place at baseline, three months (post assessment) and twelve months (follow-up assessment) after baseline assessment. The study design and participant flow are outlined in the Consolidated Standards for Reporting Trials (CONSORT) diagram (Fig. 1). After giving informed consent and completion of the baseline survey, participants will be randomly assigned to the intervention or control group. In the intervention group, participants will receive telephone counselling from counsellors of the national German Smokers Quitline, while in the control group they will be provided with a self-help brochure to support smoking cessation. Self-help materials were chosen as treatment in the control condition, as participants may have a benefit compared to receiving no intervention [20]. Moreover, it is considered unethical to recruit participants for a smoking cessation treatment when subsequently not offering an intervention. Providing an alternative intervention for the control group may also help achieve comparable response rates. To allow correction for any overreporting of abstinence, abstinence will be biochemically verified for a random sample of study participants who report abstinence at 12-month follow-up.

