### Data collection and management

Participants will be recruited consecutively between October 2021 and June 2022. Therefore, data collection will take place at different time points (at baseline, three months and twelve months after baseline assessment) over a period of approximately two years. Data will be collected via online questionnaires using the software SoSci Survey [46]. It is expected that the majority of questionnaires will be administered digitally (compared to phone interviews). In order to biochemically verify abstinence, 20% of study participants who will report abstinence at 12-month follow-up and who consented to participate will be randomly selected. Research staff will meet participants at their preferred location and will collect breath carbon monoxide (CO) using a portable CO monitor.

Once a participant is enrolled, the study site will make every reasonable effort to follow the participant for the entire study period. Various procedures will be used to reduce attrition, including reminder emails and calls, flexible scheduling of the counselling sessions, and incentives for completing the questionnaires. It is expected that the rate of loss-to-follow-up will not exceed the calculated 30%. To enhance validity of data, multiple methods will be used to assess intervention adherence including the phone call prior to enrolment in order to answer possible questions and questionnaire items on the use and acceptability of the received intervention at 3-month post assessment.

All participant data is handled in accordance with the General Data Protection Regulation (GDPR). All data will be maintained confidentially before, during, and after the trial and is stored securely at the study site with access only by dedicated study team members. All substantial procedures are described in the application for the Ethics Committee and can be provided on request. The final data set will be stored for 10 years after completion of the study. A data monitoring committee is not considered necessary as participants are not blinded to the study conditions and as this is a short-term, non-invasive intervention with the opportunity to quit at any time without any negative consequences or side-effects.

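### Three abstinence measures and a 20% CO subsample are all called primary with no ranking or success rule, while the sample size rests on one 5% test

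*Protocol article*

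**What the plan says.** **Primary outcomes.** Under this heading the protocol article states: "primary outcome measures will include (1) seven-day point prevalence abstinence at 3-month post and 12-month follow-up assessment, (2) prolonged abstinence". Prolonged abstinence is defined as "abstinence over the 12 month period allowing up to five cigarettes in total". A third numbered item is "biochemical verification of abstinence in 20% of the abstainers at 12-month follow-up", with an 8 ppm CO cut-off for defining abstinence. Item (1) holds two time points, so there are three abstinence comparisons plus CO.

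**Abstract, Methods.** The list is shorter here: "Primary outcome measures will include the seven-day point prevalence abstinence at 3-month and 12-month assessments as well as prolonged abstinence". CO is not in it.

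**Sample size calculation.** The target of 700 (350 per arm), raised to 910, is based on 7-day abstinence with a small effect, 5% significance and power 0.8. Neither the time point nor the sidedness is given.

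**Statistical analyses.** Cessation rates are to be compared by logistic regression and analysis of variance. No outcome is put first.

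**Role of CO.** Study design gives the purpose: "To allow correction for any overreporting of abstinence, abstinence will be biochemically verified for a random sample of study participants". The Discussion likewise presents the subsample as a guard against reporting bias.

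**CO sampling.** The note to Table 1 describes a "20% random sample of participants who reported 7-day point prevalence abstinence at 12-month assessment". Data collection and management says instead that "20% of study participants who will report abstinence at 12-month follow-up and who consented to participate will be randomly selected".

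**The concern.** The trial is sized for one test but has three abstinence results that could each be reported as its primary finding. Without a ranking or a success rule, that choice can be made after the data are seen, and the 5% level no longer describes the chance of a false primary claim.

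The CO item raises a separate problem. It is measured only in people who report abstinence, and in a fifth of those, so it cannot compare the randomised groups. Its stated purpose is to check or correct self-report. Allocation is unblinded and abstinence is self-reported, so that check matters. A draw made only from people who have already agreed may miss some of the misreporting it is meant to find.

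**Working it through.** **1. The plan's own figure.** 700 × 1.30 = 910, as stated. The 350 per arm cannot be reproduced, because the effect is described only as small. At two-sided 5% and 80% power, a standardised effect of 0.2 needs 393 per arm (310 one-sided). This failure to reproduce does not prove an error. What matters here is that the calculation allows for one test at one 5% level.

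**2. Familywise error, any one of three tests sufficing.** Assume no true effect and each test at two-sided 5%.

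- Independent tests, either direction: 1 − 0.95³ = 0.143.
- Independent tests, in favour of counselling: 1 − 0.975³ = 0.073. One test gives 0.025.

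The three outcomes are positively correlated, since people with prolonged abstinence are largely a subset of those abstinent at each assessment. Simulation of three normal test statistics with equal correlation (2 million draws) gives:

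| Correlation | Either direction | In favour of counselling |
|---|---|---|
| 0 | 14.3% | 7.3% |
| 0.3 | 13.6% | 6.8% |
| 0.5 | 12.5% | 6.2% |
| 0.7 | 11.0% | 5.5% |
| 0.8 | 9.8% | 4.9% |
| 0.9 | 8.4% | 4.2% |

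The documents do not give the correlation. As an assumption, take prolonged abstinence as nested in both point-prevalence measures, with 3-month rates of 10–25%, 12-month rates of 7–20% and prolonged rates of 3–10%. The results are then 11.1–13.2% in either direction and 5.5–6.6% in favour of counselling. If the tests were one-sided at 5%, the same simulation gives a false claim of benefit in 14.3% at correlation 0 and 9.3% at 0.8.

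If all three tests must be significant, the error cannot exceed that of a single test.

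**3. Size of the CO subsample.** There are 910 / 2 = 455 people per arm. The quit rates come from the Background.

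- Long-term rates in the cited systematic review, 7% vs 10%: 455 × 0.07 × 0.2 = 6.4 and 455 × 0.10 × 0.2 = 9.1, or about 6 and 9 people.
- 3-month rates in the earlier non-randomised evaluation, 11.1% vs 22.3%: 455 × 0.111 × 0.2 = 10.1 and 455 × 0.223 × 0.2 = 20.3, or about 10 and 20 people.

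The precision can be shown without assuming a misreporting rate. Suppose everyone tested is verified. The exact 95% lower limit for the verified proportion is 0.025^(1/n): 54% for n = 6, 66% for n = 9, 69% for n = 10 and 83% for n = 20. Even a perfect result would leave substantial, and different, misreporting in the two arms possible.

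**4. The sampling frame.** Study design and the Table 1 note draw from people who report abstinence. Data collection and management draws from those who report abstinence and have consented. Under the second rule, someone who over-reports and declines never enters the draw and is not seen as a refusal. If people are drawn first and asked afterwards, the refusal is visible and can be counted.

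**5. Power of the first test in a sequence.** Take 7% vs 10%, 455 per arm and two-sided 5%. The null standard error is √(2 × 0.085 × 0.915 / 455) = 0.01849. The alternative standard error is √((0.07 × 0.93 + 0.10 × 0.90) / 455) = 0.01846. Power = Φ((0.03 − 1.96 × 0.01849) / 0.01846) = Φ(−0.34) = 0.37.

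**The case against.** **The error rate is conditional.** No section says that one significant result is enough. The Abstract and Discussion expect higher cessation at both three and twelve months, and if all tests had to succeed there would be no inflation. This stands as a limit on the number. It does not rescue the plan, because an expectation is not a decision rule.

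**Direction.** A reader might infer a 10–14% chance of wrongly declaring the quitline effective. With two-sided tests that figure counts errors in both directions, and the chance of a false claim of benefit is about 5–7%. Sidedness is not stated, so the stronger reading cannot be asserted.

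**An analysis plan may control alpha.** It may, and no missing procedure is held against the article. The point rests on what the article fixes: several unranked primaries set against a one-test sample size.

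**CO is mainly a labelling slip.** Largely true. The Abstract leaves CO out of the primary list, and Study design and the Discussion treat it as a check. The sections still need reconciling.

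**Consent is unavoidable.** Table 1 marks informed consent at the CO visit, so the table does not contradict the idea of consent. What is unsettled is whether consent comes before or after the draw, and how refusals count. A reader might go further and infer that the verification will make self-report look valid. The documents give no refusal or misreporting rate, and the €30 payment and visits at a place of the participant's choice may raise uptake. The bias is possible but not shown. Nor do the documents promise a correction by arm; step 3 shows only that the numbers could not support one.

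**Conclusion.** The concern holds in this limited form. The article makes three abstinence comparisons and a CO subsample primary without ranking them, against a sample size built on one 5% test with no time point.

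If any one of three two-sided 5% tests counts as success, the familywise error is about 10–14% for correlations from 0 to 0.8, and about 5–7% in favour of counselling against 2.5% for one test. Above a correlation of 0.8 it falls below 10%. CO does not enter these figures.

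CO verification is not a randomised comparison, and calling it primary conflicts with the Abstract, Study design and the Discussion. Drawing only from those who consented can bias the check towards confirming self-report; by how much cannot be determined from the document.

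**What to change.** **Ranking.** Before outcome data are seen, name one primary outcome and time point. 7-day abstinence at 12 months by intention to treat fits the Sample size calculation and the Discussion's argument for a 12-month assessment. The choice is the trial team's, and that argument could also support prolonged abstinence. Test the others in a stated fixed sequence at 5%, or state that all must succeed.

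**CO.** Reclassify it as a validation measure, consistently in every section. Draw the 20% at random from all self-reported abstainers, within each arm and before asking for consent. Count refusals as not verified. Report verified rates by arm with exact confidence intervals, and use them only in a sensitivity analysis.

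**Cost.** The changes are to wording, with no added participants or CO visits. A 3-month-only effect could no longer be claimed as primary success. If the first test fails, the later outcomes are descriptive only; at 7% vs 10% its power is about 37%, so failure would be more likely than success. Requiring all to succeed is no cheaper, since its power cannot exceed that of the weakest test. A Bonferroni split (0.05 / 3 = 0.0167 each) would cut power from 80% to about 66% for the effect that 350 per arm can detect, or need 467 evaluable per arm to restore it.

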#### Secondary outcomes

Among participants who report being non-abstinent at 3- and 12-month follow-up, secondary outcome measures will include: (1) changes in number of cigarettes smoked per day and in nicotine dependence levels [30], (2) the number and duration of quit attempts after intervention start [31, 32], (3) the occurrence of abstinence of at least 24 hours at some point during the study (4), [31] an increase in motivation to quit (5), [33] the implementation of smoking restrictions at home [34]. A change in smoking-related cognitions (smoking outcome expectancies [35, 36]; self-efficacy to refrain from smoking [36–38]; self-efficacy for abstinence [39]) and coping strategies (avoidance of external cues [40]; perceived control over withdrawal symptoms [41]) will be assessed among all participants.

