Germany implemented its national Smokers Quitline in 1999. It is overseen by the Federal Centre for Health Education [‘Bundeszentrale für gesundheitliche Aufklärung, BZgA’] and offers reactive telephone counselling (calls initiated by the smoker) with a maximum of five proactive follow-up calls (calls initiated by the counsellor). Trained specialists advise smokers seeking support in smoking cessation, former smokers experiencing a relapse crisis, and information seekers who intend to quit. In 2021, more than 33,000 German smokers contacted the national Smokers Quitline. In a previous evaluation, it was found that smokers who received proactive counselling (several counselling sessions) from the national German Smokers Quitline had significantly higher abstinence rates three months after the intervention than smokers who received reactive counselling (one-time counselling) (22.3% vs. 11.1%) [19]. In this study, participants were not randomly assigned to one of the two study conditions.

As the impact of the national German Smokers Quitline could be increased by optimizing the offered intervention, the overall goal of the current study is to conduct a two-arm randomized controlled trial to evaluate the effectiveness of the national German Smokers Quitline. To accomplish this, abstinence rates will be compared among smokers, who will receive proactive telephone counselling and smokers who will receive a self-help brochure. Based on previous research [15], we expect higher smoking cessation rates among participants in the telephone counselling condition compared to the control condition (primary outcome). In addition, we hypothesize that telephone counselling will increase quit attempts, the occurrence of 24-hour abstinence, the motivation to quit, the implementation of smoking restrictions at home, and reduce daily cigarette consumption and nicotine dependence levels among non-abstainers three and twelve months after start of the intervention (secondary outcomes).

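### Six secondary outcomes are compared between arms only among participants still smoking at follow-up, a group defined after randomisation by the primary outcome; for 24-hour abstinence and any quit attempt this removes certain successes

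*Protocol article*

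**What the plan says.** The section on secondary outcomes in the protocol article begins "Among participants who report being non-abstinent at 3- and 12-month follow-up, secondary outcome measures will include". The list that follows contains "changes in number of cigarettes smoked per day and in nicotine dependence levels", "the number and duration of quit attempts after intervention start", "the occurrence of abstinence of at least 24 hours at some point during the study", motivation to quit and home smoking restrictions. Smoking-related cognitions and coping strategies are treated differently: change in these "will be assessed among all participants".

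The Abstract repeats the restriction ("Among non-abstainers, treatment success indicators such as a reduction in number of cigarettes smoked per day"). The Background states a directional hypothesis that counselling will, among other things, "reduce daily cigarette consumption and nicotine dependence levels among non-abstainers three and twelve months after start of the intervention", and the Discussion repeats it. Read alone, that sentence might attach the restriction only to consumption and dependence, but the section on secondary outcomes attaches it to the whole list.

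The section on statistical analyses states the intention-to-treat rule, with undetermined smoking status counted as smoking, for abstinence rates. No section calls the non-abstainer comparisons descriptive, adds a version in all randomised participants, or names the restriction among the limitations.

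**The concern.** Seven-day abstinence at 3 and 12 months is a primary outcome, and the trial is built on the expectation that counselling raises it. Restricting a secondary comparison to people who are not abstinent selects on that outcome after randomisation. If the primary hypothesis is true, counselling turns some participants into abstainers who would have kept smoking under the brochure. They leave the counselling subset while their counterparts stay in the control subset, so the two subsets no longer differ by treatment alone.

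For two outcomes the selection acts directly on the result. A person abstinent for the past seven days has been abstinent for 24 hours. A daily smoker at enrolment who is now abstinent has stopped smoking. The plan therefore discards participants who are certain successes on 24-hour abstinence and on any quit attempt. At stake is whether the hypothesised secondary benefits can be read as effects of counselling.

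**Working it through.** The plan gives no figure for these outcomes, so there is none to reproduce. The check asks what the restricted comparison shows when the truth in all randomised participants is known.

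**Inputs**
- Abstinence, lower case: 7% control, 10% counselling. Background, from the systematic review of proactive calls against self-help or brief counselling, long-term.
- Abstinence, upper illustration: 11.1% and 22.3%. Background, from the earlier non-randomised evaluation of reactive against proactive counselling at three months.
- True proportion reaching 24-hour abstinence in all randomised participants: not given. Assumed 60%, with a range of 40% to 60%.
- Full follow-up is assumed, and one assessment is taken at a time.

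**Formula.** Let r be the proportion of all randomised participants with at least 24 hours of abstinence and p the proportion abstinent at follow-up. All abstainers are included in r, so the proportion among non-abstainers is (r − p)/(1 − p).

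**No true difference, r = 60% in both arms**
- Lower case: control (0.60 − 0.07)/0.93 = 57.0%; counselling (0.60 − 0.10)/0.90 = 55.6%; difference −1.4 points.
- Upper illustration: control (0.60 − 0.111)/0.889 = 55.0%; counselling (0.60 − 0.223)/0.777 = 48.5%; difference −6.5 points.

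Over the assumed range (differences taken from unrounded values):

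| r, both arms | 7% vs 10% abstinent | 11.1% vs 22.3% abstinent |
|---|---|---|
| 40% | 35.5% vs 33.3%, −2.2 | 32.5% vs 22.8%, −9.7 |
| 50% | 46.2% vs 44.4%, −1.8 | 43.8% vs 35.6%, −8.1 |
| 60% | 57.0% vs 55.6%, −1.4 | 55.0% vs 48.5%, −6.5 |

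**A true benefit**
- 60% to 65%, upper illustration: (0.65 − 0.223)/0.777 = 55.0% against 55.0% in control, so the gain disappears.
- 50% to 55%, upper illustration: 43.8% vs 42.1%, so a true +5.0 becomes −1.7.
- 60% to 65%, lower case: 57.0% vs 61.1%, so +5.0 becomes +4.1.
- 60% to 75%, lower case: 57.0% vs 72.2%, so +15.0 becomes +15.2. With a large true effect and a small abstinence difference, the distortion is negligible.

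**Size against sampling error.** Take the 350 per arm from the sample size section and r = 60%. In the lower case, 350 × 0.93 = 325.5 and 350 × 0.90 = 315 non-abstainers remain. The standard error is √(0.570 × 0.430/325.5 + 0.556 × 0.444/315) = 3.9 points, so a bias of 1.4 is under 0.4 standard errors. In the upper illustration, 311 and 272 remain, the standard error is 4.1 points, and 6.5 is about 1.6 standard errors.

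**Other outcomes.** No identity applies, so a simulation was run under a chosen mechanism: counselling has no effect on a standardised smoking measure, and lighter smokers quit first. With assumed correlations of 0.3 to 0.7 between the measure and the propensity to quit, the two-sided 5% test rejects in 5.4% to 7.6% of trials in the lower case and in 9.7% to 36.0% in the upper illustration. These figures depend on the assumed mechanism, for which the document gives no evidence.

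**The case against.** The strongest defence is that little is harmed. Only secondary outcomes are involved, and the abstinence analysis keeps all randomised participants. The best-matched rates in the document are 7% vs 10%, where the false harm is 1.4 points and well inside sampling error. The large figures come from a comparison that was not randomised, ran to three months and had no self-help arm. All of this stands and limits the size of the point.

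The authors may also want to know whether continuing smokers benefit. That is a fair question, but the observed non-abstainers in each arm do not answer it causally. The analysis plan, not shown, might add an all-randomised version. The protocol nevertheless fixes the population and states hypotheses of effect in it, so its text needs changing either way.

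A reader might infer that every hypothesised secondary benefit is biased toward no effect or harm. The document does not support that. For cigarettes per day, dependence, motivation and home restrictions, direction depends on who quits, and everyone enrolled already intends to quit within a month. The number of attempts can go either way: someone who succeeds at the first try has one attempt, and someone who keeps failing may have several.

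A reader might also fault the plan because non-responders count as smokers in the primary analysis but are absent here. Counting missing as smoking supplies no cigarette count or dependence score, so a different population for those measures is unavoidable.

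**Conclusion.** The point holds for the six restricted outcomes: the planned arm comparisons condition on the primary outcome and are not randomised comparisons if counselling works. For 24-hour abstinence and any quit attempt, certain successes are dropped, and with no true difference the result always leans against the arm with more abstainers. With r assumed at 40% to 60%, the false harm is 1.4 to 2.2 points at 7% vs 10%, and 6.5 to 9.7 points at the upper illustration. With r held fixed, it grows as the abstinence rates separate. For the remaining outcomes, including the number and duration of attempts, the comparison is not protected by randomisation, but size and direction are unknown. Conclusions on abstinence, cognitions and coping are untouched. This merits correction before analysis; it does not threaten the trial's main result.

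**What to change.** - Test 24-hour abstinence and any quit attempt (yes/no) between arms in all randomised participants, with the exclusions already allowed for the abstinence analysis. Count abstainers as yes. State a rule for non-responders, for example counted as no, in line with the section on statistical analyses, with a responder-only sensitivity analysis.
- Compare home smoking restrictions, and cigarettes per day with abstainers set to 0, among all participants with follow-up data.
- Keep the non-abstainer results for cigarettes per day, dependence, number and duration of attempts, and motivation as descriptive, without causal claims. Motivation to quit has no obvious value for an abstainer, and the number and duration of attempts cannot be filled in by definition.
- Reword the hypotheses in the Background and Discussion to match.

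The cost is small. Table 1 schedules these measures at 3 and 12 months and shows no restriction to non-abstainers, and the abstainers' values for 24-hour abstinence, any quit attempt and current cigarettes follow from their status. Check that the questionnaire asks abstainers about home restrictions. There is a real trade-off: cigarettes per day in everyone partly restates the abstinence result, and the question about continuing smokers becomes descriptive. The choice should be fixed before outcome data are analysed by arm.
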